# Efficacy and Safety of Ginkgo Biloba Pills for Coronary Heart Disease with Impaired Glucose Regulation: Study Protocol for a Series of* N*-of-1 Randomized, Double-Blind, Placebo-Controlled Trials

**DOI:** 10.1155/2018/7571629

**Published:** 2018-10-14

## Abstract

**Background:**

Coronary heart disease has become a serious challenge to China with its high prevalence and mortality. The impaired glucose regulation is prevalent in patients with cardiovascular disease. However, there are few drugs that interfere early with impaired glucose regulation. Ginkgo biloba extract not only is a commonly used drug for cardiovascular diseases, but also has a significant effect in reducing blood sugar. Therefore, this study used a single-case randomized controlled trial to explore the efficacy of Ginkgo biloba pills in the treatment of coronary heart disease patients with impaired glucose regulation.

**Methods/Design:**

This is a randomized, double-blind, placebo-controlled, three-period crossover trial for a single subject. A total of 12 subjects will be recruited in this trial. The trial is divided into three cycles, and one cycle has two treatment periods. Ginkgo biloba pills and placebo will be randomized during the treatment period. The test period will last for 58 weeks and subjects will take 48 weeks. Subjects will be selected by the researcher strictly in accordance with the inclusion and exclusion criteria.

**Discussion:**

Ginkgo biloba preparations are widely used in cardiovascular diseases both at home and abroad due to their definite curative effect, few side effects, various dosage forms, and convenient and safe use. Diabetes mellitus is a high-risk factor for the occurrence of cardiovascular disease. Therefore, it is of great significance to control the impaired glucose regulation and slow down the development of diabetes and reduce the incidence and mortality of cardiovascular diseases. This trial is registered with ClinicalTrials.gov (ID: NCT03483779).

## 1. Background

With the development of economy and the improvement of living standards, the prevalence and mortality of coronary atherosclerotic heart disease (CHD) have been significantly higher than before and have been more in younger age in China. The global disease burden report [1], which was published in the Lancet in 2015, showed CHD ranked second in the cause of death in the Chinese population in 2013. Therefore, cardiovascular disease is a serious challenge for China's public health and health care.

As we all know, diabetes is one of the important independent dangerous factors for CHD, and almost all patients with type 2 diabetes experience a prediabetic stage, which is usually characterized by impaired fasting glucose, impaired glucose tolerance, etc. This stage is medically known as impaired glucose regulation (IGR). The crowd at this stage is characterized by blood glucose levels that are already above the normal range, but have not yet met the criteria for diabetes. At the European Society of Cardiology Annual Meeting 2004, the European Heart Survey released the first results of a survey on the state of glucose metabolism in patients with CHD. Studies have shown that about two-thirds of patients with CHD have diabetes or IGR [2]. The findings further demonstrate the cross-coexistence relationship between diabetes and cardiovascular disease and also indicate that IGR is prevalent in patients with cardiovascular disease. The U.S. Bureau of Health Care Research and Quality conducted a systematic review of 156 prediabetes studies [3], suggesting that prediabetes is associated with a higher risk of diabetes and cardiovascular disease, and early identification and treatment of prediabetic patients may reduce or delay the progression of diabetes and its associated cardiovascular complications and microvascular disease. Therefore, we should take effective measures to intervene in prediabetes in a timely manner.

At present, early treatment of IGR is mainly based on lifestyle interventions, including health education, diet therapy, exercise therapy, weight control, and smoking cessation and abstinence. However, lifestyle interventions in the actual living environment are effective, but poor patient compliance and clinically continuous and strict follow-up often fail to achieve the desired effect [4]. Some clinical trials have also confirmed the effectiveness of drug interventions such as acarbose, metformin, and other drugs [5]. The drugs selected for IGR should meet the requirements of long-term use, no serious adverse reactions, no hypoglycemia, and other conditions, but, at present, there are few related drug researches, and the choice of drugs is relatively limited in clinical applications.

## 2. Ginkgo Biloba

Ginkgo biloba is a leaf of Ginkgo biloba L., which has attracted much attention due to its high medicinal value. In traditional Chinese medicine, Ginkgo biloba is considered to be flat, sweet, bitter, and astringent, and it has the function of promoting blood circulation and removing blood stasis, removing obstruction in the channels to stop pain, astringing Lung-Qi and relieving cough and melting turbidity and reducing lipid decoction. It is commonly used in the treatment of obstruction of collaterals by blood stasis, chest stuffiness and pains, apoplectic hemiplegia, etc. [6]. Since the 1960s, with the in-depth study of the chemical constituents of Ginkgo biloba by domestic and foreign scholars, their pharmacological effects and clinical applications have been under further understanding.

Related studies have shown that the effective medicinal components extracted from Ginkgo biloba are mainly flavonoids, terpene lactones, and organic acids, which increase blood flow, prevent blood clots, reduce blood lipids, regulate the central nervous system, improve memory function, and improve cognitive function. The known pharmacological effects are mainly related to the mechanisms of antagonizing platelet activating factor (PAF), antioxidation, scavenging free radicals, and regulating the release of excitatory amino acids [7]. Current research shows that insulin resistance and insulin secretion deficiency are the main pathogeneses of diabetes, and Ginkgo biloba extract (EGb) has a bidirectional role in regulating insulin secretion. On the one hand, it can improve hyperinsulinemia in patients with insulin resistance. On the other hand, it can increase insulin secretion in patients with impaired islet function, and its mechanism of action is mainly to protect *β*-cells, promote insulin secretion, reduce free fatty acid (FFA) levels, inhibit activation of inflammatory factors, increase adiponectin, decrease leptin levels, and activate glucose transporter 4 to improve insulin resistance [8].

More studies [9] confirmed the hypoglycemic effect of EGb. Daye Cheng et al. [10] administered streptozotocin-induced diabetic rats with high, medium, and low doses of EGb. After 30 days of treatment, the blood glucose level in the different doses of EGb treatment group was significantly lower than that in the control group. The blood glucose level in the high-dose EGb group decreased to the normal range, and its hypoglycemic effect was significantly dose and time dependent. Clinical studies have found that EGb can improve insulin resistance in patients with CHD and have the effect of regulating blood glucose and lipid metabolism [11]. Studies of EGb intervening in db/db diabetic mice have shown that EGb can significantly reduce fasting blood glucose in db/db diabetic mice by increasing the islet mass, reducing the level of oxidative stress in the pancreatic islets, significantly reducing fasting blood glucose in db/db diabetic mice, improving insulin sensitivity, and improving glucose tolerance and beta-cell secretion, especially early phase insulin secretion [12]. Our previous study also found that EGb pretreatment can reduce myocardial injury induced by acute myocardial ischemia in type 2 diabetic rats, and its cardiovascular protection may be closely related to the activation of actin clearance system [13].

## 3. Why N-of-1 Trials

The single-case randomized controlled (N-of-1) trials were designed for a single patient or a series of individual patients, with multiple prospective clinical randomized crossover trials alternating between multiple trials and controls [14]. [name] of McMaster University in Canada pointed out that in the latest evidence pyramid, the single-case randomized controlled trial is at the highest level of clinical research evidence, and the systematic review of randomized controlled trials is in second place [15]. N-of-1 trial is a clinical efficacy evaluation method that meets the self-regulation and characteristics of the individual medical treatment in traditional Chinese medicine (TCM). The study of N-of-1 for TCM can highlight individualized diagnosis and treatment and maintain TCM characteristics. It can also make the clinical research of TCM more scientific and can avoid the influence of subjective selection, implementation and measurement bias, and individual differences, especially for chronic diseases requiring long-term treatment. Therefore, in this study, patients with CHD and IGR will be selected as the study subjects. N-of-1 trials will be used to evaluate the clinical efficacy of Ginkgo biloba pills and to explore the individualized therapeutic evaluation methods applicable to TCM research.

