## 4. Methods

### 4.1. Trial Design

This is a randomized, double-blind, placebo-controlled, single-case clinical trial in which each subject can be considered as having its own RCT. Twelve subjects with CHD associated with IGR will be screened. Each N-of-1 trial will consist of 3 cycles, including 6 treatment periods, 2 of which are in one group, including 8 weeks of placebo treatment and 8 weeks of Ginkgo biloba. Each subject took Ginkgo biloba drop pills or Ginkgo biloba drop pills simulant at random. There was no washout period at the beginning of the study and there was a 2-week washout period before each treatment period. The entire experimental observation time window is 58 weeks ± 5 days.  Table 1 shows the study design of the subject's medication process. The protocol conforms to the Standard Protocol Items: CONSORT extension for reporting N-of-1 trials (CENT) 2015 [16]. The CENT 2015 checklist can be found in Additional file 2.

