### 4.13. Statistical Methods

Statistical analysis software will use SAS statistical analysis software version 9.4.

The results were analyzed at the end of the test. The description of the quantitative indicators will calculate the mean, standard deviation, median, minimum, maximum, and interquartile range. The description of qualitative indicators will calculate the number of cases and percentage of each category. All statistical tests use two-sided tests. When the* P* value is less than or equal to 0.05, the difference is considered statistically significant (except where specifically stated). Descriptive statistics will be performed on the completion of the study. Demographics and baseline characteristics will be compared between groups to analyze the balance between the groups.

The analysis of efficacy indicators will use Revman5.0 software for meta-analysis.

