## 5. Discussion

A single-case randomized controlled trial used a single subject as the study subject. Under the same specified conditions, the differences between different individuals were observed. This was in line with the differences between Chinese medicine and syndrome differentiation. Impaired sugar regulation is generally rarely treated in clinical practice. Doctors generally recommend that patients actively engage in various lifestyle interventions in order to prevent the rise of blood glucose. If the patient does not intervene or the intervention fails, which leads to the rise of blood glucose to diabetes, it worsens the patient's pain and condition. This study selected patients with coronary heart disease and IGR as research subjects to evaluate the efficacy of Ginkgo biloba pills in the treatment of coronary heart disease with glucose regulation. Patients with this disease can be provided with a new treatment idea. This study can be viewed as an exploratory study, using small samples to conduct experiments, thus saving manpower, material resources, and financial resources.

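### Individualised evaluation is one of the two stated aims, but the only efficacy method named is a RevMan meta-analysis, which targets the average effect and whose patient-level by-products are unreliable with three pairs per patient

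*Protocol article*

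**What the plan says.** - **Aims.** Section 3 closes with two. The first is to judge whether the pills work. The second is "to explore the individualized therapeutic evaluation methods applicable to TCM research".
- **Design.** Section 4.1 describes a "single-case clinical trial in which each subject can be considered as having its own RCT". It adds: "Each N-of-1 trial will consist of 3 cycles, including 6 treatment periods". Each cycle pairs one Ginkgo period with one placebo period.
- **Size.** The abstract states: "A total of 12 subjects will be recruited in this trial". No effect size, SD or power accompanies the number.
- **Rationale.** Section 5, describing single-case trials, says that "the differences between different individuals were observed".
- **Analysis.** On efficacy, Section 4.13 has one sentence: "The analysis of efficacy indicators will use Revman5.0 software for meta-analysis". It does not give the unit entered as a study, the model (fixed or random effects) or any patient-level output. The same section names SAS 9.4 as the statistical software.

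**The concern.** A design with repeated randomised pairs in each patient is the one that can separate true differences between patients from period-to-period noise. A standard meta-analysis answers the first aim. For the second it offers only by-products: a row per patient on a forest plot, and Q or I². A reader would naturally use the rows to sort patients into responders and non-responders, and I² to judge whether effects differ. If both are mostly noise with three pairs per patient, the individual aim is not merely unanswered but may be answered wrongly. The data for a sound answer will have been collected over 58 weeks per patient.

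**Working it through.** **Inputs from the document.** 12 patients, 3 cycles of 2 periods, so 3 pairs per patient and 12 × 3 = 36 pairs. The timetable is consistent: 6 × 8 = 48 weeks on treatment and 48 + 5 × 2 = 58 weeks in all, as stated. The sample size cannot be reproduced, because no basis for it is given.

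**Assumptions.** Sigma is the SD of one end-of-period value and tau the SD of true effects between patients. Errors are normal with equal variance, there is no carryover, and each period gives one value. Neither SD is in the document, so results are in sigma units over a range of tau. Simulations used 20,000 to 40,000 trials.

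**1. Precision of one patient's raw difference.**
- A paired difference has variance 2 sigma². The mean of three has variance 2/3 = 0.67 sigma², which is its mean squared error (MSE) for that patient's true effect.
- The interval uses t(0.975, 2 df) = 4.303, so its half-width is 4.303 × √(2/3) = 3.51 sigma when the SD equals its true value. The average is 3.11 sigma, since an SD on 2 df averages 0.886 of the truth (3.51 × 0.886).
- If every patient had the same true benefit of 0.5 sigma, a raw difference would have the wrong sign with probability Φ(−0.5/√0.667) = Φ(−0.61) = 27%.

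**2. Heterogeneity output with patients as studies.** Q = Σ wᵢ(dᵢ − d̄)², with wᵢ = 1/SEᵢ², is referred to chi-square on 11 df. This treats each SE as known. With tau = 0, so no true difference between patients:

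| SE used | Q rejects at 5% | Median I² |
|---|---|---|
| Paired (2 df) | about 64% | about 57% |
| Unpaired, 3 against 3 | about 35% | about 30% |

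The patient-by-treatment F test with pooled within-patient variance (11 and 24 df) rejects in 5.0% on the same data.

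**3. Three ways to estimate a patient's own effect.** MSE in sigma²:

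| tau | Raw difference | Pooled mean | Shrunken (tau estimated by moments) |
|---|---|---|---|
| 0.25 sigma | 0.67 | 0.11 | 0.16 |
| 0.5 sigma | 0.67 | 0.29 | 0.28 |
| 1 sigma | 0.67 | 0.97 | 0.48 |

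The pooled-mean column follows from tau² × 11/12 + 0.667/12. At tau = 0.5 that is 0.229 + 0.056 = 0.285; at tau = 1 it is 0.917 + 0.056 = 0.972.

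**4. Limits of the remedy.**
- The moment estimate of tau is zero in 46% of trials at tau = 0.25 sigma and 30% at 0.5 sigma. All 12 shrunken estimates then equal the pooled mean.
- Simple plug-in 95% intervals around shrunken estimates cover 92%, 86% and 89% at tau = 0.25, 0.5 and 1 sigma.
- The F test has power of 16% at tau = 0.5 sigma and 57% at tau = sigma.

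**The case against.** The document is a condensed article. Section 4.13 does not say that only an average will be reported, and a fuller protocol or analysis plan may add individual analyses. A reader might infer that the trial collapses everything into a single average and returns no individual result. The text does not support that: the unit is not stated, and a meta-analysis with patients as studies needs per-patient estimates and normally prints a heterogeneity statistic. What stands is narrower. The one method named targets the average, and its by-products are unfit for the second aim.

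The second aim is also modest. It is to explore methods, the abstract states efficacy alone, Section 5 calls the study exploratory, and Section 3 elsewhere treats individual differences as something the design avoids. This limits the weight of the point. It does not remove an aim that the article states and uses to justify the design.

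A further temptation is to fault the pooled interval for missing individual effects. A confidence interval for a mean does not claim to contain them, so that is no defect.

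The strongest statistical objection also stands in part. At tau = 0.25 sigma the pooled mean predicts a patient's effect better than shrinkage (0.11 against 0.16), and at 0.5 sigma they practically tie. The case for shrinkage over the pooled mean therefore depends on a large tau. Its case against raw differences does not: it wins at all three values.

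**Conclusion.** The point holds as a mismatch between a stated aim and the only stated efficacy method. It should be corrected before unblinding, but it does not invalidate the average-effect analysis as a target. The firmest figures are those that need no value of tau: raw-difference MSE of 0.67 sigma² on 2 df, and false heterogeneity in about 64% or 35% of trials when patients do not differ. These assume that patients are the meta-analysis units, with normal errors and no carryover. The gain from shrinkage is conditional. Against raw differences, MSE falls from 0.67 to 0.16, 0.28 and 0.48 sigma² at tau = 0.25, 0.5 and 1 sigma. Against the pooled mean, the gain is clear only near tau = sigma (0.48 against 0.97).

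**What to change.** In Section 4.13, keep the average effect and add, in SAS 9.4, for each primary outcome:

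1. One mixed model for all period values, with patient, cycle within patient, treatment, a random patient-by-treatment effect and a common within-patient variance. Code the random effect as a treatment slope, so that its SD is the SD of the Ginkgo-placebo difference. If it is coded with one independent term per arm, the variance of the difference is twice that component.
2. Report the mean effect, the between-patient SD of the effect with its interval, and each patient's shrunken difference with an interval that allows for uncertainty in that SD. Kenward-Roger or a Bayesian hierarchical fit are examples; a plug-in interval is not adequate.
3. State that no patient will be labelled a responder or non-responder from a raw three-pair difference, and that RevMan I² will not be used to judge whether effects differ.
4. State the limits: with 12 patients the between-patient SD is imprecise and its estimate will often be zero, in which case every shrunken estimate equals the mean.

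The cost is a paragraph of analysis text and one model per primary outcome. No new data, visits or patients are needed.

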## 4. Methods

### 4.1. Trial Design

This is a randomized, double-blind, placebo-controlled, single-case clinical trial in which each subject can be considered as having its own RCT. Twelve subjects with CHD associated with IGR will be screened. Each N-of-1 trial will consist of 3 cycles, including 6 treatment periods, 2 of which are in one group, including 8 weeks of placebo treatment and 8 weeks of Ginkgo biloba. Each subject took Ginkgo biloba drop pills or Ginkgo biloba drop pills simulant at random. There was no washout period at the beginning of the study and there was a 2-week washout period before each treatment period. The entire experimental observation time window is 58 weeks ± 5 days.  Table 1 shows the study design of the subject's medication process. The protocol conforms to the Standard Protocol Items: CONSORT extension for reporting N-of-1 trials (CENT) 2015 [16]. The CENT 2015 checklist can be found in Additional file 2.

### 4.2. Study Participants

All patients participating in the experiment should be screened strictly in accordance with the following criteria.

#### 4.2.1. Diagnostic Criteria

*(1) Diagnostic Criteria for Coronary Heart Disease*. According to the 2010 Guidelines for the Diagnosis and Treatment of Clinical Coronary Heart Diseases.

(a) Clear history of old myocardial infarction, or a history of PCI, or a history of CABG (at least 3 months).

(b) Coronary angiography or coronary CTA results suggesting that at least one coronary branch is stenotic and the degree of stenosis is ≥50%.

*(2) Diagnostic Criteria for Stable Angina*. According to the Chinese Medical Association, Cardiovascular Branch, the Chinese Journal of Cardiovascular Diseases Editors Committee 2007 Guidelines for the Diagnosis and Treatment of Chronic Stable Angina.

The main content is that when there is physical activity or mental stress, coronary blood flow cannot meet the needs of myocardial metabolism, leading to myocardial ischemia-induced angina pectoris, and rest or nitroglycerin can be relieved. Chronic stable angina patient is a patient whose degree, frequency, nature, and predisposing factors of angina pectoris have not changed significantly within 1 to 3 months.

*(3) Impaired Glucose Regulation (Prediabetes) Diagnostic Criteria*. According to the 2016 American Diabetes Association (ADA) diagnostic criteria: impaired fasting glucose regulation (IFG); fasting blood glucose (FPG) 5.6 ~ 6.9mmol/L, or glucose tolerance decrease (IGT); 2 h blood glucose (2hPG) 7.8 to 11.0mmol/L after oral administration of 75g glucose in OGTT, or glycosylated hemoglobin (HbA1c) in 5.7% to 6.4 %.

*(4) Diagnostic Criteria for Blood Stasis Syndrome*. According to the “Diagnostic Criteria for Coronary Heart Disease and Blood Stasis Syndrome” promulgated by the Professional Committee for the Promotion of Blood and Blood Stasis of the Chinese Association of Integrative Medicine in China in 2016.

#### 4.2.2. Inclusion Criteria

Participants fulfill the following inclusion criteria: (1) male and female patients with clear history of previous myocardial infarction or history of percutaneous coronary intervention (PCI) or history of coronary artery bypass grafting (CABG) (at least 3 months or more), or who have coronary angiography or coronary CT angiography (CTA) results suggesting at least one coronary artery stenosis and lumen stenosis ≥ 50%, (2) in line with the criteria for stable angina, and the number of episodes of angina pectoris ≥ 2 times per week, (3) complying with the diagnostic criteria of blood stasis syndrome of coronary heart disease (CHD), (4) complying with the 2016 Diabetes Association (ADA) published criteria for impaired diagnosis of glucose regulation, and (5) aging between 18 and 75 years. Participants voluntarily participated in this study, signed informed consent, and had good compliance.

